## **3. STUDY DESIGN**

The study will be conducted over twelve months in the Cardiac Intensive Care Unit at Hammersmith Hospital, Imperial College Healthcare NHS Trust. For this study, a total of 30 individuals (12 patients, 12 family members or close friends and 6 critical care nurses) will be recruited and interviewed to allow sufficient depth and richness of data. Patients and family members/friends will be mainly recruited from the ICHT pre-operative clinic outpatient department, which runs several pre-operative clinics per week. Each week, approximately eight patients undergo cardiac surgery, and the research team intends to recruit one patient and their family member/friend per a week for a period of 4 months.

All participants will be given time to consider their participation in the study and if happy will be consented by PI or other delegated member of the research team. Patients will be approached during one of their pre-operative clinic appointments and informed consent will be sought at this stage. Once written consent has been obtained, patients will be asked to nominate a family member or friend to be contacted by the PI. After signing the consent form, family members/friends will also be enrolled into the study and requested to self-record short videos pre-operatively (based on a guided script - ANNEX XIII), which will be safely uploaded to an iPad. In addition, patients will be requested to select multiple pictures, which will be securely uploaded into a digital photo frame. This package combination of videos and pictures will be shown to patients post-operatively in ICU. Critical care nurses will be recruited after they have provided direct care to at least one participant, who received the study intervention in ICU.

This is a mixed methods research study including the collection of data from patient's medical notes, interviews and quality of life questionnaires in accordance with the schedule of assessments (SoA, Annex I). This study also involves the implementation of an auditory-visual sensory stimulation package in the cardiac ICU at ICHT to participants enrolled in the study. Digital photos will be shown continuously at the patient bedside after cardiac surgery and will always have reference to time and date. Additionally, videos will be played throughout participants' stay in ICU for at least three times per day and upon participant request. Videos will be also played when participant show signs of ICU delirium with the aim of reducing delirium incidence and improve overall better health outcomes. Simultaneously, primary outcomes measures (CAM-ICU, a routine delirium screening measure) will be collected by the research team, as this is evaluated twice a day as per usual standard of ICU practice, with the aim of assessing whether patients develop delirium during their stay in ICU.

Interviews with patients and families/friends will be held in three different occasions. The first one will be on the same day as ICU discharge, the second interview will be on the day of hospital discharge and the third one will be carried out up to a month following hospital discharge during their clinical follow-up appointment. Where possible, family members/friend and patient's interviews will be conducted together (dyadic interviewing), but the possibility of performing interviews separately will be given, so that participants feel able to discuss opinions freely without influence. Nurses' interviews will be held as a one-off and after they have provided direct care to participants who received the proposed intervention.

Each patient will be followed up daily on the wards and once at the monthly follow-up clinic up after ICU discharge, where cognitive and emotional assessments will be performed to evaluate delirium outcomes. The research team will also collect relevant information from participant's medical notes if any complications post ICU discharge arise during inpatient and follow-up stages.

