In occasions where participants are unable to consent or have lost their capacity to consent more than once whilst in ICU (e.g., delirium), their participation in the study will be considered by approaching their personal consultee. If their participation in the study resumes, videos / photos will be played at the patients' bedside during the planned intervention schedule. Upon delirium diagnosis, the last video played will be shown again to patients with the aim of promoting a reduction in ICU delirium. In the unfortunate eventuality of an urgent clinical deterioration (e.g., urgent induced coma due to mechanical ventilation requirements) that may happen whilst in ICU, their participation in the study will also resume considering their initial consent form signed before surgery and after seeking prior agreement with their personal consultee. In these situations, the Patient Regaining Capacity Consent Form will be collected at a later stage and after patients have re-gained capacity to express their wishes.

For patients who lose mental capacity after hospital discharge, they will be formally discussed with the CI and withdrawn from the research study. The study team will communicate the decision to participants and appropriately document it on medical notes.

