### Personal Consultees

Personal consultees, who are interested in the patient's welfare but not doing so for remuneration or acting in a professional capacity, will be included in this research study. Consultees can be anyone within the patient's family or friend's group (e.g. relative/friend/partner). When possible, patients will delegate pre-operatively whom they would like to select as personal consultee.

Consultees will be introduced to the study post-operatively and in situations where patients lack capacity to verbalise their wishes (e.g., delirium). They will be given time to consider their role in the study and they will be provided with a study information sheet. If they agree to act as personal consultees for this study, the research team will ask them to consider whether patients would wish to continue taking part in the study or not. When an unanimous decision (between the research team and consultees) has been made, this will be clearly documented on patients' medical notes and consultees will be asked to sign a consent form.

If consultees agree that patients should continue in the study, their participation will resume. However, if personal consultees believe participants should be withdrawn from the study, the research team will respect their decision and make any necessary arrangements.

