## **6. STUDY ASSESSMENTS**

### **6.1. ASSESSMENT AND FOLLOW UP**

#### **STUDY INTERVENTION**

The intervention will require family members/friends (selected by patients) to self-record short videos (during the preoperative stage) based on a carefully drafted guided script divided into two parts: a) Reorientation (discussing date/time/surroundings, family members on the video); b) Reassurance (providing comforting/supportive messages). Videos will be recorded either with a video-recorder device (provided by the research team) in the pre-operative clinic or at home using a personal smartphone. At a later stage, videos will be sent to an encrypted NHS email and securely uploaded in line with ICHT Information Governance to a password-protected iPad, which will also facilitate family-patient video calls in ICU. In addition, patients will be requested to select personal pictures pre-operatively, which will be also sent to the PI's encrypted NHS email and securely uploaded into a special digital photo frame with reference to time and date.

Digital photos will be shown continuously at the patient's bedside for 12 hours a day (between 8am to 8pm) and different family videos will be played three times at specific hours of the day (9am, 2pm and 7pm) throughout their stay in ICU. Additionally, videos will be also played upon patient request and last video shown that day will be re-played. In occasions when patients develop ICU delirium and considering personal consultee's agreement, the last video shown to participants will be re-played and patients will be closely monitored. This will help the research team to understand if the combination of personal pictures and family videos impacted patients' orientation and reassurance and if, ultimately, promoted the reduction of ICU delirium. The PI will be responsible for setting up the required equipment and delivering the intervention alongside ICU nurses as illustrated in the study diagram below (Annex XI).

The draft guided script of reorientation and reassurance messages was initially developed based on published research and considering patients' memories from their lived ICU experience(s) [15]. Subsequently, it was further refined within a lay focus group of patient and public members (with ICU lived experience) and reviewed by an expert panel comprising two critical

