| 5 | Did the patient look at the digital photo frame during the day?                                     |  Yes  No
If “Yes”, how many times: ____                                                                                                                                                                                     |
| 6 | Did the intervention impact ICU nursing care?                                                       |  Yes  No
If “Yes”, please specify: ____                                                                                                                                                                                     |
| 7 | Was the family intervention delivered without any untoward events (eg., acute distress)?            |  Yes  No
If “No”, please specify: ____                                                                                                                                                                                      |
| 8 | Did the patient request to watch the video more than 3 times a day?                                 |  Yes  No
If “Yes”, please specify the total number of times: ____                                                                                                                                                           |
| 9 | Did the patient develop delirium during the day (8am-8pm)?                                          |  Yes  No
9a. If “Yes”, was the video played again?
 Yes  No
9b. If “Yes”, did it improve delirium status?
 Yes  No |

Table 2. Nursing Checklist Night-time

| N | Nursing Checklist Night-time (8pm – 8am)                          | Tick as appropriate                                                                                                                                                                                                                                                            |

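### The delirium-triggered video replay has two different triggers in the protocol, and the nurse checklist cannot tell a missed replay from one that was not due

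*Protocol*

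**What the plan says.** Three places in the protocol govern the replay given because of delirium.

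- Section 3 (Study Design): "Videos will be also played when participant show signs of ICU delirium". The sentence names neither a diagnosis nor a consultee.
- Section 4.6 (Patients Regaining Consent): "Upon delirium diagnosis, the last video played will be shown again to patients". The same paragraph first requires the personal consultee to be approached for patients who cannot consent in ICU, and then says "If their participation in the study resumes, videos / photos will be played at the patients' bedside during the planned intervention schedule".
- Section 6.1 (Study Intervention): "In occasions when patients develop ICU delirium and considering personal consultee's agreement, the last video shown to participants will be re-played".

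The Personal Consultees part of section 4.6 introduces consultees to the study after surgery, when the patient lacks capacity, and allows them time to consider. Section 3 states that CAM-ICU is assessed twice daily.

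Delivery is recorded on the Annex XII checklist, by shift. Daytime item 9 and night-time item 4 ask whether delirium developed. If it did, 9a and 4a ask "was the video played again", with Yes and No as the only answers. Items 9b and 4b then ask whether delirium status improved.

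**The concern.** The endpoint in section 3.1 is the feasibility and acceptability of delivering the intervention, and section 6.1 has ICU nurses delivering it alongside the investigator. For a component delivered at the bedside, nurses need one statement of when it is due, and the analysis needs a record of whether it was given when due.

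Neither is secured for the replay. A nurse working from section 3 would act on signs. A nurse working from 4.6 or 6.1 would wait for diagnosed or developed delirium and for the consultee step. The same omitted replay is then a failure of delivery under one reading and correct conduct under the other, and the form gives both the same tick. The trigger used also decides which episodes are replayed, and hence which supply an answer to 9b and 4b.

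**Working it through.** There is no protocol figure to reproduce. The check sets the rules beside the form.

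**Step 1: how many rules?** Sections 4.6 and 6.1 both replay the last video, both concern a patient who has delirium, and both place the consultee before the replay. They can be read as one rule. Section 3 differs in the event (signs) and is silent on the consultee. That leaves two rules, with no statement of precedence.

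**Step 2: what does each rule require, and what does the form show?**

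| Situation | Section 3 sentence alone | Sections 4.6 and 6.1 together | Checklist entry |
|---|---|---|---|
| Signs only, no replay | due | not yet due | item 9 is 'No' and 9a is blank, or item 9 is 'Yes' and 9a is 'No', depending on what the nurse counts as delirium |
| Delirium diagnosed, consultee not yet agreed, no replay | due | not due | 9 'Yes', 9a 'No' |
| Delirium diagnosed, consultee agreed, no replay | due | due, missed | 9 'Yes', 9a 'No' |
| Delirium diagnosed, consultee agreed, replay given | due | due, delivered | 9 'Yes', 9a 'Yes', 9b answered |

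The second and third rows have identical entries although only the third is a missed delivery under 4.6 and 6.1. The first row can look the same, because item 9 does not say whether delirium means signs or a positive CAM-ICU. Night-time items 4, 4a and 4b behave in the same way.

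**Step 3: can the situations arise?** Signs can appear at any time, while formal screening is twice daily. If the two screens were evenly spaced, which the protocol does not say, diagnosis could follow signs by up to 24 / 2 = 12 hours. Section 4.5 has the patient choose a consultee at recruitment, but under section 4.6 the consultee is brought into the study only after surgery and with time to reflect. A first delirium episode can therefore precede agreement.

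**Step 4: could the form carry the missing information?** Yes. Daytime item 2 already offers N/A, item 3 asks for clock times, and items 4, 6 and 7 ask for details. Items 9a and 4a have none of these.

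**Step 5: scale.** Section 7 sets 12 patients. Section 1.1 cites up to 55% delirium after cardiac surgery: 12 × 0.55 = 6.6, or about 7 patients expected at that upper rate. Section 1.1 gives no lower bound for cardiac surgery. Its general ICU range of 30-80% would give 12 × 0.30 = 3.6 to 12 × 0.80 = 9.6.

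**The case against.** The strongest reply is that section 3 is an overview and the detailed sections control. Several parts of this stand.

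- A reader might infer three conflicting triggers. The text does not support that, since 4.6 and 6.1 are compatible.
- A reader might infer that section 3 allows a replay to a patient without capacity and without the consultee. It does not. Section 8.2 brings in a consultee whenever capacity is lost and treats consent as ongoing before any study task, and 4.6 applies the consultee step to the scheduled videos and photos as well. Silence in section 3 does not waive those rules.
- A reader might infer that a replay-rate endpoint is distorted by a calculable number of percentage points. The protocol defines no such endpoint or threshold. The form works by shift, so one reclassified shift need not reclassify a patient.
- A reader might infer that the reason for a 'No' is lost altogether. Consultee decisions go into the medical notes and onto a signed form, CAM-ICU results are taken from the records, and deviations are logged. With 12 patients, consultee status on a delirious shift can largely be looked up.

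What the reply does not answer is the event itself. Nothing says that section 3 yields to the later sections, and signs versus diagnosis is a real difference for the nurse delivering the replay. No planned field records that signs prompted, or failed to prompt, a replay, so that part may not be recoverable afterwards.

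**Conclusion.** The point holds in limited form. The protocol gives two triggers for the delirium replay, signs in section 3 and diagnosed or developed delirium behind the consultee step in 4.6 and 6.1, without saying which governs. Taken alone, the checklist cannot separate a missed replay from one not due, and it collects response only for episodes that were replayed.

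The size is modest. The scheduled three-times-daily videos and the photo display are outside the point. About 7 of 12 patients would be expected to reach the rule at the cited cardiac upper rate. That count assumes the cited rate applies at this unit, and the 12-hour figure assumes evenly spaced screens; the conclusion depends on neither. It rests on the wording of the three sections and the two form items. It is worth correcting before recruitment because feasibility of delivery is what the study sets out to measure.

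**What to change.** 1. Reconcile sections 3, 4.6 and 6.1 into a single trigger, worded identically in all three places, with a cross-reference to the consultee rule. Which trigger to adopt is a clinical matter for the study team.
2. State on the checklist what counts as delirium in items 9 and 4, in line with the reconciled trigger.
3. At items 9a and 4a, record the trigger and its time. For a 'No', add a reason or a not-due option that includes consultee agreement not being in place.
4. Describe replay delivery among episodes in which a replay was due under the reconciled rule, and report the not-due episodes separately. Present 9b and 4b as describing replayed episodes only.

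The cost is a protocol wording change, a few entries on an existing form, and slightly more nurse recording on delirious shifts. No extra assessment or patient contact is needed.

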### **3.1. STUDY OUTCOME MEASURES**

The study's endpoint, similar to the primary objective of this research study, is to assess the feasibility and acceptability of implementing a nurse-led intervention in ICU, using family-focused sensory stimulation to improve delirium outcomes in patients undergoing cardiac surgery.

This study secondary outcome measures are to develop an innovative nurse-led tool to improve ICU delirium outcomes after cardiac surgery in ICHT and its acceptance amongst patients, family members/friends and critical care staff.

#### **4. PARTICIPANT ENTRY**

Recruitment and screening activities will be mainly carried out by the study PI, who is currently funded to support research in the department led by the care team. The PI will aim to work together with the surgical team and when appropriate, add clinicians to the delegation log, such as doctors in clinic. This will allow the supporting clinical team members to refer potential participants to the research team.

##### **4.1. PRE-REGISTRATION EVALUATIONS**

Potential eligible participants will be identified by the PI and pre-operative surgical team responsible for their care. All participants will be discussed regularly with the research team to ensure their suitability for the study. Before eligibility is established, PI will remotely screen participant's electronic medical notes, diagnostics tests and/or attend multidisciplinary team meeting minutes to confirm participants' suitability to undergo major cardiac surgery.

##### **4.2. INCLUSION CRITERIA**

###### **PARTICIPANTS**

- Female and male patients over the age of 18
- Participants speaking English language and having mental capacity to consent
- Suitable to undergoing cardiac surgery at ICHT.

###### **FAMILY MEMBERS/FRIENDS**

- Nominated by the participant.
- Be willing to record videos and participate in the study.

###### **HEALTHCARE PROFESSIONALS**

- Critical Care Nurses that have provided direct care to at least one patient who received the study intervention

##### **4.3. EXCLUSION CRITERIA**

###### **PARTICIPANTS**

- Female and male patients under the age of 18
- Unable to consent to the study pre-operatively
- Significant hearing/visual impairment
- Participants with learning disabilities, pre-existing delirium, dementia or other significant underlying cognitive morbidity
- Moribund participants, likely to die in the next 24 hours
- Participants that do not speak English language

###### **FAMILY MEMBERS/FRIENDS**

- Refuse to consent or gain assent
- Significant hearing/visual impairment

- Family members/friends that do not speak English language

#### HEALTHCARE PROFESSIONALS

- Critical care nurses that have not been involved in the implementation of the intervention
- Refuse to consent or gain assent
- Significant hearing/visual impairment and non-English speaking

### **4.4. WITHDRAWAL CRITERIA**

#### PARTICIPANTS WITHDRAWAL CRITERIA

- No longer willing to participate after consent
- Personal consultee wishing to withdraw participants from the study
- Patients that the clinical and/or research team deem too distressed to continue participating in the study
- Participants who have lost capacity to participate in the study after hospital discharge

For participants wishing to not continue in the research study their decision will be respected. Participants will be reassured that their wishes will not affect their care and/or employment in any way. They will also be informed that they are not required to give a reason with regard to not wishing to participate. However, if they are happy, the reason will be recorded in their medical records.

When conducting clinical research, the study team will always respect participants' interests and prioritise them over those of science and society. Therefore, if the participant wishes to be withdrawn from the study, this must be done without delay and appropriately documented in the medical notes. The research team will respect participants' wishes and feelings by ensuring that no study activities are done to and/or carried out in relation to participants who object to continuing in the study. Those participants wishing to withdraw will be asked for permission to keep the data already collected, but if they decline, all data will be destroyed appropriately.

The study team will also assume the professional responsibility to protect participants from the risk of harm and/or prevent them from feeling pain or discomfort. Additionally, the Principal Investigator in agreement with the Chief Investigator will also consider withdrawing any participant who appears to be in too much distress throughout the research study. If so, this will be discussed with the participant and clearly documented on medical notes.

Participants who lose capacity after hospital discharge or die unexpectedly during the course of the study will be automatically withdrawn. If they are withdrawn, any identifiable data already collected with consent will be retained and may be analysed, but no further data will be collected, or any other research procedures carried out in relation to these patients.

